## Abstract

**Introduction::**

Obesity is a global public health issue, which results in many health complications. Moxibustion may serve as an alternative management for simple obesity, where pharmacological therapy is always difficult to be accepted by the majority of obese patients based on its safety. However, the effects of herb-partitioned moxibustion as obesity intervention have not been confirmed. This study is designed as a single-blinded, 3-dummy randomized controlled trial to evaluate the efficacy and safety of herb-partitioned moxibustion plus lifestyle modification treatment in patients with simple obesity.

**Methods and analysis::**

This study will be a randomized, controlled trial conducted from April, 2019 to April, 2021 that includes 108 participants who have simple obesity and meet the eligibility criteria. The participants will be randomly divided into 3 treatment groups: heat application group, medicated plaster group, or herb-partitioned moxibustion group. Each treatment will last 4 weeks. The primary outcomes will be the clinical effectiveness. The secondary outcome measures include participants’ obesity-related indicators, the IWQOL-Lite scale, and the syndrome score of Traditional Chinese Medicine. Adverse events will be recorded during the intervention period.

**Ethics and dissemination::**

Ethical approval of this study was granted by the Ethics Committee of Hubei Provincial Hospital of Traditional Chinese Medicine on 15 November 2018 (Ethics Reference No: HBZY2018-C24-01). Written informed consents will be provided by all participants before they were enrolled in this study.

**Trial registration number::**

NCT04606680

## Introduction

1

Obesity, which is resulted from a broken energy homeostasis, is defined as an excessive or abnormal fat accumulation.^[1,2]^ Epidemiological surveys show that obesity has a continuously increasing trend worldwide.^[3,4]^ In 2016, there were over 1.9 billion adults overweight. In the United States, at least 78.6 million people are suffering from obesity.^[5]^ According to WHO, around 2.8 million people die annually due to overweight or obesity. It has been reported that obesity increased the incidence and risks of disorders and diseases such as cardiovascular disease, type 2 diabetes mellitus, neurodegenerative diseases, liver disease, and even cancer, in particular Alzheimer disease.^[6–8]^ In addition, not only the obesity epidemic has a major impact on people's health but many risk factors can also increase obesity prevalence based on the complexity of its pathophysiology, metabolic consequences, and mechanisms.^[9,10]^ Nowadays, overweight and obesity have become an epidemic of the 21st century due to the speed of its development. Research is underway around the world for a better understanding of the pathogenesis and etiology of obesity.

As part of traditional Chinese medicine (TCM), moxibustion interventions have been widely used in clinical practice. Recent studies have shown that moxibustion is effective in adjusting the levels of fat accumulation, blood lipids, and female sex hormones.^[11,12]^ For example, a Chinese research showed that moxibustion stimulates the patient's intestinal micro ecology system by stimulating related acupoints, accelerates the lipid metabolism in the endocrine system and corrects gut microbes disorders, thereby achieving the effect of weight loss.^[13]^ Several studies in animal models have also demonstrated the positive effects of moxibustion in patients with endocrine issues and excess body weight. Specifically, Zhu and colleagues found that moxibustion significantly decreased total plasma cholesterol and slowed the rate of body weight gain in 14-month-old rats when compared with the control group.^[14]^ Overall, these findings suggest that moxibustion has a positive impact on both body weight and blood lipids management. It has become more and more popular with patients and doctors based on its unique advantages of effectiveness, simplicity, and convenience.

To date, there are no studies on the effect of a combined application of herb-partitioned moxibustion plus lifestyle modification treatment in patients with simple obesity. We will conduct a 3-arm parallel clinical trial. In this study, our aim is to investigate the effects of a combined application of herb-partitioned moxibustion plus lifestyle modification treatment in terms of obesity-related indicators, the syndrome score of TCM, and the improvement of the quality of life in patients with simple obesity. We hypothesize that a combination of partitioned moxibustion plus lifestyle modification treatment will produce more beneficial results than the application of these therapies alone in addressing obesity symptoms.

## Methods and analysis

2

### Study design

2.1

This trial is designed as a prospective, outcome-assessor-blinded, parallel-arm, single-center (Hubei Provincial Hospital of TCM, China), randomized controlled clinical trial with a 1:1:1 allocation ratio to evaluate the efficacy of herb-partitioned moxibustion plus lifestyle modification treatment for patients with simple obesity. A total of 108 participants, who meet the inclusion and exclusion criteria, will be randomly allocated to heat application group, medicated plaster group, or herb-partitioned moxibustion group (n = 36 each). The patients will receive these treatments once per day, 3 d/wk for 4 weeks. The flow diagram of the study procedure is showed in Figure 1. Participants’ recruiting is from April 2019.

**Figure 1 F1:**
[figure not shown]
Flow diagram of the study procedure.

### Recruitment

2.2

Trial participants with simple obesity will be recruited at the Hubei Provincial Hospital of TCM in China. The study will be advertised through the internet, posters, and local newspapers in hospitals and communities. The study procedure will be informed to those interested individuals who want to participate in this clinical trial through visits to our hospital or telephone calls. During visits to our hospital, the participants who meet the inclusion and exclusion criteria will be asked to voluntarily sign an informed consent form before participation. Every time the enrolled participant visits, the clinicians of outpatient clinics in our hospital will tell them the next visit's schedule and remind them of the schedule by telephone the day before the visit. In addition, the medical condition of enrolled participants will be continuously monitored by the clinical research coordinator to ensure adherence to the intervention protocols.

### Study procedure

2.3

This study consists of 2 phases including:

(1)a 4-week screening phase (week 0);(2)a 4-week treatment phase (week 1–4).

When potential participants show interest in this study, they will be instructed to record their medical history in a screening form. Thereafter, they will be invited to complete an eligibility assessment by trial investigators; next, eligible participants will be enrolled and written informed consent will be provided to them. Participants who meet the inclusion criteria and exclusion criteria will be enrolled, grouped, and given a 4-week interventions. The schedule of enrolments, allocation and assessments is given in Table 1 below.

**Table 1 T1:** The schedule of enrolments, allocation, and assessments.

Phase	Enrolment/allocation	The treatment period			
Timepoint	Wk 0	Wk 1	Wk 2	Wk 3	Wk 4
Informed consent	X				
Eligibility screening	X				
Demographic data	X				
Obesity-related indicators	X	X	X	X	X
The IWQOL-Lite scale	X	X	X	X	X
The syndrome score of TCM	X	X	X	X	X
Record of treatment		X	X	X	X
Drug combination∗	X				
Adverse event	X				
Compliance evaluation	X				
Research completion	X				
Investigator review	X				
Supervisor review	X				

### Participants

2.4

#### Diagnostic criteria

2.4.1

(1)Body mass index (BMI): BMI = weight (kg)/height (m^2^), according to the criteria about the weight division of Asian adults in the Redefine and Processing of Obesity in Asia Pacific issued by WHO in February 2000: BMI ≥ 23 for overweight, BMI between 23 and 24.9 for the early stage of obesity, BMI between 23 and 24.9 for I degree of obesity, BMI ≥ 30 for II degree of obesity.(2)Waist circumference (WC): WC ≥90 cm for male and 80 cm for female.

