#### Inclusion criteria

2.4.2

Participants meeting all of the following criteria will be considered for inclusion:

(1)diagnosed as having simple obesity according to the diagnostic criteria;(2)aged between 18 and 45 years old;(3)Waistline: male≥ 95 cm, women≥85 cm;(4)Being able to fully understand and voluntarily sign informed consent.

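### The BMI bands behind inclusion criterion 1 print 23–24.9 for two obesity grades and none for 25–29.9, so the BMI needed for entry is not fixed

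*Protocol article*

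**What the plan says.** Section 2.4.1 of the protocol article (Diagnostic criteria) has two numbered items. The first grades BMI and names a WHO Asia-Pacific document of February 2000 as its source. It gives four labels in one sentence: "BMI ≥ 23 for overweight", then "BMI between 23 and 24.9 for the early stage of obesity, BMI between 23 and 24.9 for I degree of obesity", then "BMI ≥ 30 for II degree of obesity". The second item is a waist limit: "WC ≥90 cm for male and 80 cm for female".

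Section 2.4.2 (Inclusion criteria) requires all of its criteria to be met. The first is that the patient is "diagnosed as having simple obesity according to the diagnostic criteria". The third is a separate waist limit: "Waistline: male≥ 95 cm, women≥85 cm". The other two concern age (18 to 45 years) and consent. Section 2.4.2 gives no BMI value of its own. Elsewhere BMI appears only as an outcome (sections 2.8.2.1 and 2.12).

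**The concern.** The early-stage and degree I grades carry the same band, and the next grade starts at 30. Read literally, a patient with BMI 24 has degree I obesity and a patient with BMI 28 has no grade of obesity. A grading in which a higher BMI loses the diagnosis cannot be what was meant.

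This would be a minor slip in a background paragraph, but here inclusion criterion 1 points to it. Section 2.5 leaves it to attending physicians to identify eligible patients. Under different readings they could turn away patients in the ungraded range, or admit patients whom the same sentence calls overweight. A reader of the results could not tell which population was randomised. The per-protocol analysis in section 2.12 also could not be checked for eligibility violations on BMI.

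**Working it through.** No formula for power or sample size is involved. The check is whether the printed bands cover the BMI scale once and only once.

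**Inputs (all from section 2.4.1).** Overweight: 23 and above, no upper limit. Early stage: 23 to 24.9. Degree I: 23 to 24.9. Degree II: 30 and above.

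**Step 1: assign each BMI from 22.0 to 32.0, in steps of 0.1, to every band as printed.**

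| BMI | Overweight | Early stage | Degree I | Degree II | Obesity grades held |
|---|---|---|---|---|---|
| below 23 | no | no | no | no | 0 |
| 23.0–24.9 | yes | yes | yes | no | 2 |
| 25.0–29.9 | yes | no | no | no | 0 |
| 30.0 and above | yes | no | no | yes | 1 |

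The number of obesity grades held runs 0, 2, 0, 1 as BMI rises. The ungraded range is 30 − 25 = 5 BMI units wide and lies between two ranges that are graded.

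**Step 2: see what entry threshold follows.** Criterion 1 asks for simple obesity, but section 2.4.1 does not say which grade qualifies. Three readings are open:

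- 23, if the lowest label containing the word obesity is enough;
- 25, if degree I is the first qualifying grade and is assumed to have been meant for the unassigned range;
- 30, if only the one grade with a band of its own is trusted.

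**Step 3: test whether repairing the duplicate would be enough.** As an assumption only, since the documents do not give this band, put degree I at 25–29.9. At one decimal the three obesity grades then do not overlap and cover every BMI from 23 upward. That fits a transcription slip, but the documents cannot confirm it. It also leaves 23–24.9 both overweight and early-stage obesity, so it is still not stated whether such a patient qualifies.

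**Step 4: test whether the waist limits settle it.** The two sets differ by 95 − 90 = 5 cm for men and 85 − 80 = 5 cm for women. Taking the female limit in section 2.4.1 as a minimum too, anyone who meets criterion 3 already meets the diagnostic waist limit. Section 2.4.1 does not say whether its BMI and waist items are both needed. If both are, the BMI bands decide entry and the ambiguity stands in full. If either suffices, criterion 3 would already confer the diagnosis and the BMI bands would exclude nobody. The waist limits therefore do not supply a BMI threshold, and the link between the two items is open as well.

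**The case against.** The strongest reply is that this is a plain copying error with little practical effect. The lowest obesity label starts at 23 and the highest is open-ended from 30, so no sensible screener would enrol patients at 24 and 31 and refuse one at 28. The section also names its source, which site staff can consult. Every participant must in any case pass a legible and stricter waist limit. Much of this stands: refusal of the middle range is unlikely in practice, and the live question is the entry floor. But repairing the duplicate does not answer that question (step 3), and neither do the waist limits (step 4). Nor is this a matter of a journal article leaving detail to a fuller document, because the article states the bands and states them wrongly.

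Four stronger readings are tempting, and the documents do not support them:

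- **That eligibility as a whole is undefined.** The age and waist limits are clear; only the BMI part is not.
- **That 25–29.9 is wholly unclassified.** It has no obesity grade, but it does fall under "BMI ≥ 23 for overweight".
- **That the secondary outcome called obesity degree is misgraded by these bands.** Section 2.12 lists it among the continuous variables, summarised by mean and standard deviation, and nothing ties it to section 2.4.1.
- **That the comparison between arms is biased.** Eligibility is settled before allocation and in the same way for all three arms. The primary outcome in section 2.8.1 is built on percentage change in the syndrome score and uses no BMI band.

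**Conclusion.** The BMI part of eligibility is wrong as written. One band, 23–24.9, carries two grades; a range of five units, 25–29.9, carries none; and the minimum BMI for entry can be read as 23, 25 or 30. The consequence falls on the definition of the enrolled population and on generalisability, not on the treatment comparison.

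The conclusion rests on the sections as printed and on the fact that no other part of the article gives a BMI cut-off for entry. How far the bands decide entry depends on whether the BMI item is required for the diagnosis, which the article leaves unsaid. The share of patients affected cannot be estimated, because no BMI distribution is given. Which band or threshold is right is for the sponsor to establish from the named source. Because the trial relies on this rule to select patients and the correction is cheap, it should be made.

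**What to change.** 1. In section 2.4.1, reconcile the bands with the guideline named there, so that the obesity grades neither overlap nor leave a gap. Say whether overweight is an umbrella label over the grades.
2. In section 2.4.2, state as a numbered criterion the single minimum BMI that qualifies as simple obesity.
3. Say whether the BMI and waist items in section 2.4.1 are both required, and reconcile the 90/80 cm limits there with the 95/85 cm limits in section 2.4.2.
4. Recruitment is dated from April 2019 (section 2.1), so check the BMI of participants already enrolled against the corrected criterion.

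The cost is a few lines of text and one pass through the baseline data. The small downside is that a few enrolled participants may fall outside the corrected criterion; a sensitivity analysis without them would then be needed. The obesity degree outcome needs no change on this account.

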#### Inclusion criteria

2.4.2

Participants meeting all of the following criteria will be considered for inclusion:

(1)diagnosed as having simple obesity according to the diagnostic criteria;(2)aged between 18 and 45 years old;(3)Waistline: male≥ 95 cm, women≥85 cm;(4)Being able to fully understand and voluntarily sign informed consent.

#### Exclusion criteria

2.4.3

Participants will be excluded if they have

(1)Presence of endocrine disorders such as: polycystic ovary syndrome; Cushing syndrome; uncorrected thyroid disease.(2)Presence of diabetes mellitus, or hypertension, or abnormal liver and kidney functions, or mental diseases.^[15]^(3)Pregnant or lactating state, women who plan to become pregnant within 4 weeks.(4)History of bulimia, anorexia, or any other eating disorders.^[16]^(5)Use of medications in the past 3 months, such as diet drugs, corticosteroids, antidepressants, which may affect weight or appetite.(6)History of surgical weight loss, postoperative adhesions.(7)History of participating in a clinical study of weight loss or any other therapies to lose weight in the past 3 months.(8)Presence of local skin rupture, allergy, and scar constitution.(9)Unable to cooperate with the research caused by other diseases or reasons.

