#### Lifestyle modification treatment

2.7.1

The following lifestyle modification are recommended to help to establish healthy habits:

(1)firstly, the basal metabolic value of patients will be calculated based on the formula of BMR according to body weight recommended by FAQ/WHO;(2)according to the basic metabolic value, we can get the difference between the daily intake of diet calories and exercise consumption calories, that is: the intake of dietary calories-exercise consumption of calories ≤ the basic metabolic value;(3)according to the difference between the calculated dietary calories and exercise calories, all participants will be prescribed an appropriate diet and exercise programs, which is formulated according to requirements of dietary guidelines for Chinese residents approved and issued by the Standing Council of Chinese Nutrition Society. The proportion of 3 nutrients in total calories comprises of 55% to 65% from carbohydrates, 20% to 30% from oils and 15% from protein, and the energy of the whole day distributed to 3 meals will follow the proportion of 30% for breakfast, 40% for lunch, and 30% for dinner. Meanwhile, all participants will be instructed to record their food and calorie intake daily, and low-to-moderate intensity physical activities such as jogging, walking, and swimming will be instructed to them for at least 5 days per week continually, 30% to 50% of the maximum heart rate reserve value will be required. The maximum heart rate reserve value = the patient's maximum heart rate (220-age)-the patient's static heart rate (the heart rate when the patient wakes up in the morning but has not yet got up).

All patients will be instructed to keep a diet and exercise diary.

The intervention time of lifestyle modification treatment will last for 8 weeks.

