#### Heat application group

2.7.2

The acupoints will be selected as Tianshu, Pishu, shenshu, zhongwan, and zusanli. The location of the acupoints were based on the national GB/T 12346-2006 acupoints standard.^[17]^ The hot sticker will be placed on the patient's acupoints for about 2 hours. This treatment will be applied once every other day, 3 times per week, for 4 consecutive weeks. The treatment will be delayed during the menstrual period.

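### The 4-week pregnancy-planning exclusion covers the nominal course, but can lapse before sessions delayed for menses and before lifestyle weeks 5 to 8

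*Protocol article*

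**What the plan says.** Section 2.4.3, criterion (3), excludes pregnant and breastfeeding women and "women who plan to become pregnant within 4 weeks". It does not say from which date the 4 weeks run. Section 2.4.2 admits people "aged between 18 and 45 years old", so women of childbearing age are eligible.

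Section 2.3 describes two phases, 4 weeks of screening (labelled week 0) and 4 weeks of treatment (weeks 1 to 4). Consent and eligibility stand at week 0 in Table 1, under a phase heading that joins enrolment and allocation. The acupoint schedule is the same in all arms (sections 2.7.2 to 2.7.4): "This treatment will be applied once every other day, 3 times per week, for 4 consecutive weeks". Each of these sections then adds that treatment is put off during menstruation. None says whether, when or how quickly a postponed session is made up.

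All participants also follow the diet and exercise programme of section 2.7.1, which requires "the intake of dietary calories-exercise consumption of calories ≤ the basic metabolic value". On its length: "The intervention time of lifestyle modification treatment will last for 8 weeks". No start date is given.

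**The concern.** The 4-week figure equals the nominal treatment phase, so its evident purpose is to keep planned conception out of the period of study intervention. Two other statements in the same protocol make that period longer, or possibly longer, than 4 weeks: the postponement for menses and the 8-week lifestyle programme. A screener who applies the criterion as written could accept a woman who intends to conceive in week 5. She could then still be receiving postponed herbal or heat sessions, or following a limit on net calories.

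The stake is participant safety and the protocol's internal consistency. The protocol itself treats both pregnancy and near-term plans for it as reasons not to take part, and its dropout criteria (section 2.4.4) do not list pregnancy as a reason to stop. Nothing in the sample size or the primary analysis is at stake.

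**Working it through.** **Inputs from the protocol article**

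- Exclusion window: 4 weeks = 28 days (2.4.3).
- Course: 3 sessions per week × 4 weeks = 12 sessions, every other day (2.7.2 to 2.7.4).
- Postponement during menses in every arm, with no make-up rule (2.7.2 to 2.7.4).
- Lifestyle programme: 8 weeks, start not stated (2.7.1).
- Screening 4 weeks, treatment 4 weeks (2.3).

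**Assumptions, not in the article**

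- Day 1 is the first session and the start of the window.
- The cycle is 28 days and menses last 3 to 7 days.
- The first session falls outside menses, and every start day that allows this was tried.
- Postponed sessions are made up.

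**Step 1: nominal course.** With sessions on days 1, 3 and 5 of each week, the twelfth falls on day 21 + 5 = 26. This is inside 28 days, so the window fits the course as planned.

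**Step 2: one worked case.** Take fixed weekdays and menses on days 10 to 14. The slots on days 10 and 12 are lost. Sessions fall on days 1, 3, 5, 8, 15, 17, 19, 22, 24, 26, 29 and 31, so 2 of 12 come after day 28.

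**Step 3: all start days, at most 3 sessions per week.** The table gives the number of sessions after day 28, with the number of start days in brackets. In A, weekdays may shift, sessions are at least 2 days apart and are placed as early as possible. In B, weekdays are fixed and a missed session moves to the next free slot.

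| Menses | A: weekdays may shift | B: fixed weekdays |
|---|---|---|
| 3 days | 0 (14 of 25) or 1 (11 of 25) | 1 (18 of 25) or 2 (7 of 25) |
| 4 days | 0 (3 of 24) or 1 (21 of 24) | 1 (7 of 24) or 2 (17 of 24) |
| 5 days | 1 (16 of 23) or 2 (7 of 23) | 2 (20 of 23) or 3 (3 of 23) |
| 6 days | 1 (6 of 22) or 2 (16 of 22) | 2 (10 of 22) or 3 (12 of 22) |
| 7 days | 2 (18 of 21) or 3 (3 of 21) | 3 (21 of 21) |
| Last session | day 26 to 38 | day 29 to 40 |

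The overrun is therefore 0 to 3 of 12 sessions, and 3/12 = 25%. For menses of 3 to 4 days it is 0 to 2 sessions. For 5 to 7 days it is 1 to 3, so at least one session always falls outside.

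**Step 4: faster catch-up.** If sessions may follow every other day without the limit of 3 per week, none falls after day 28 for menses of 3 to 5 days. For 6 days it is 0 or 1, and for 7 days always 1, by day 30 at the latest.

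**Step 5: lifestyle programme.** If it starts with treatment, it ends on day 8 × 7 = 56. That is 56 − 28 = 28 days past the window, so 4 of 8 weeks are uncovered. If it starts with screening, 4 + 4 = 8 weeks and it ends with treatment, so 0 weeks run past the window.

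**The case against.** The best defence is that the window equals the stated treatment phase and that both overruns depend on things the article does not say.

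- **Make-up of sessions.** The article does not say that postponed sessions are given after week 4, Table 1 schedules nothing then, and four consecutive weeks can be read as a fixed end. A make-up rule is the kind of detail an article leaves to the full protocol. This stands to the extent that the session overrun is conditional: without make-up it is nil. But to postpone a session is not to omit it, and the criterion should not depend on which reading is used.
- **The weekly limit.** Catch-up every other day absorbs menses of 3 to 5 days (step 4). The arithmetic is right, but it needs more than the stated 3 sessions in some weeks, and 7-day menses still overrun.
- **Lifestyle start.** The two phases add up to exactly 8 weeks, which would put the programme's end at week 4. This is possible but the weaker reading, because consent, eligibility and allocation all sit at week 0 and the programme is prescribed to participants. Section 2.3 has "next, eligible participants will be enrolled" only after the eligibility assessment.
- **Harm.** The article gives no specific risk of the herbs, heat or diet in pregnancy, a coordinator monitors participants, and a woman may withdraw. That keeps the severity low. It does not make the criterion consistent with its evident purpose.

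The window's start date is also unstated. If it ran from early in screening, the gap would be larger than calculated here.

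**Conclusion.** The concern holds, at low severity. The 4-week criterion fits the nominal course counted from its start, but not the intervention with its own postponement rule, and possibly not the 8-week lifestyle component. Under the assumptions in the working, with make-up at the stated frequency, up to a quarter of the sessions fall after day 28. The lifestyle gap is 4 weeks or none, depending on when that programme starts. Which case applies cannot be settled from the article, so these are ranges and not estimates. This is a safety criterion that can admit someone it was evidently meant to exclude. It is not a flaw in the trial's inference.

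**What to change.** In section 2.4.3, criterion (3), replace the 4-week limit with: planning to become pregnant at any time from enrolment until the end of the last study intervention, including delayed sessions and the lifestyle programme. This works under every reading of the postponement rule and the lifestyle start, and it also fixes the date from which the window runs.

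The cost is a one-line amendment and a matching change to the screening form. The downside is that a few more women would be screened out.
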